### 2.6. Study Design and Planned Evaluation

The last step of IMA guides through the planning of an evaluation of the intervention programme, which for “Join the Healthy Boat” is the so-called “Health Survey.” It was designed as a prospective, stratified, cluster-randomised longitudinal trial with an intervention and a control group and is registered at the German Clinical Trials Register (DRKS), Freiburg University, Germany, ID: DRKS00010089. The study protocol was designed in 2015 and approved by the ethics committee of Ulm University (Application Number 188/15) as well as the Ministry of Culture and Education in 2016.

Participating kindergartens were recruited from all kindergartens in southwest Germany, which have received written information about programme and study, asking interested kindergarten teachers to participate. Only kindergartens which have not previously taken part in the programme were included in the study. To ensure a similar number of children in intervention and control group, stratification of randomisation was carried out on three levels on the basis of kindergarten size, that is, kindergartens with 15 or less participating children, with 16–25 participating children, and with more than 25 participating children. Therefore, 31 kindergartens were assigned to intervention group and 31 kindergartens to control group. Children within the recruited kindergartens were eligible if they were between three and five years old at the time of baseline measurements and their parents provided a signed consent form.

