### 2.7. Statistical Considerations

Further, power considerations were made prior to the study. Because of the explorative nature of this study, no adjustment for multiple testing will be made. A *p* value of less than 0.05 will be considered as significant. Subject to the number of participating kindergartens, an effect size of 0.325 (continuous outcome) can be detected with a statistical power of 0.8. The intraclass correlation coefficient was assumed as 0.05 with 40 participating children per kindergarten to reach this power. Due to the data's clustered structure, calculations will be made applying adequate statistical methods (GEE models [26]) for hierarchical data (children within kindergartens). Further details can be found in Table 1. The study's evaluation will be carried out on the basis of the intention-to-treat approach. For further assessments of effects in particular subgroups (e.g., children with migration background, overweight children) additional explorative analyses are planned. The results of all statistical tests will be interpreted in an explorative sense and not in a confirmatory way. Additionally, all main outcome variables will be adjusted for relevant socioeconomic variables (e.g., age, gender, and background).

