**Figure 3 fig3:**
[figure not shown]
Overview of recruited children, kindergartens, and kindergarten teachers, including consent for the different substudies.

**Table tab1a:** (a) Main outcomes

Outcome	Statistical analysis
Change in variables for nutrition (consumption of sugar-sweetened beverages, fruit, vegetables, high-calorie food; all variables are ordinal)	GEE model for follow-up measurement

Change in child's time spent with screen media (hours per week, ordinal/quasi-continuous variables)	GEE model for follow-up measurement

Change in child's physical activity/energy expenditure (physical activity: dichotomous, energy expenditure: continuous variables)	GEE model for follow-up measurement

Change in health knowledge and attitude of parents and kindergarten teachers (nominal/ordinal variables)	GEE model for follow-up measurement

**Table tab1b:** (b) Secondary outcomes

Outcome	Statistical analysis
Change in anthropometric parameters (waist circumference, waist-to-height ratio, BMI, subcutaneous fat; all variables are continuous)	GEE model for difference between follow-up and baseline

Change in child's quality of life (EQ5D-Y Proxy Version, KINDL parent's version; continuous variables)	GEE model for difference between follow-up and baseline

Child: change in days sick leave, doctor's consultation, hospitalisation; parents: absence from work due to children's illness (continuous variables)	GEE model for difference between follow-up and baseline

Change in child's motor skills (continuous variables)	GEE model for difference between follow-up and baseline

Environment of kindergarten and change in environment of kindergarten (continuous and categorical variables; measured on kindergarten level)	*t*-test or Wilcoxon test as appropriate, respectively, *χ*^2^-test or Fisher's exact test as appropriate for baseline and difference between follow-up and baseline

Change in laboratory parameters (saliva, cheek swab): metabolic and inflammatory parameters, for example, IL-6, TNF*α*, leptin, epigenetic investigation (continuous variables)	GEE model for difference between follow-up and baseline

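### Child-level secondary outcomes are modelled as change scores with no baseline covariate named: valid on average, but less precise than adjusting follow-up for baseline, and exposed to chance baseline imbalance

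*Protocol article*

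**What the plan says.** Table 1(b) of the protocol article gives anthropometry, quality of life, sickness and absence, motor skills and laboratory parameters the same analysis: "GEE model for difference between follow-up and baseline". The entry names no covariates. Table 1(a) treats the main outcomes differently, with a "GEE model for follow-up measurement", and names no covariates either.

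Section 2.7 adds that "all main outcome variables will be adjusted for relevant socioeconomic variables (e.g., age, gender, and background"). The baseline value of the outcome is not among the examples. Because Table 1 separates main from secondary outcomes, the sentence read literally does not reach Table 1(b).

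Two rows of Table 1(b) need separate mention. The sickness and absence row reads "Child: change in days sick leave, doctor's consultation, hospitalisation; parents: absence from work due to children's illness (continuous variables"), so quantities that are counts are labelled continuous and differenced. The row "Environment of kindergarten and change in environment of kindergarten (continuous and categorical variables; measured on kindergarten level") does not use the GEE model. It prescribes two-sample tests, applied both at baseline and to the change from baseline.

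On design, Section 2.6 describes a "prospective, stratified, cluster-randomised longitudinal trial with an intervention and a control group", in which "stratification of randomisation was carried out on three levels on the basis of kindergarten size". No child-level baseline value was balanced by design.

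**The concern.** A change score gives the baseline value a fixed weight of minus one. That weight is optimal only when baseline predicts follow-up with slope one. When the slope is lower, subtracting the whole baseline adds noise, and an arm that starts higher by chance is expected to fall back relative to the other, which the change score counts as part of the intervention effect. Regressing follow-up on baseline lets the data set the weight.

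At stake are the precision of the child-level secondary results and the credibility of any single result if the arms turn out to differ at baseline. Imbalance is a practical possibility: stratification was on kindergarten size only, and Section 3 reports that 4 of 66 kindergartens left after randomisation. The laboratory outcomes have less precision to spare, since Section 3 gives consent for 751 children for saliva and 706 for the cheek swab, against 1021 overall.

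**Working it through.** **The plan's own figure.** Section 2.7 states a detectable effect of 0.325 at power 0.80 with ICC 0.05 and 40 children per kindergarten, without giving the number of kindergartens behind it. By normal approximation it corresponds to 149 per arm × design effect [1 + 39 × 0.05 = 2.95] ≈ 440 per arm, or 11 kindergartens per arm. It says nothing about change score versus adjustment and plays no further part here.

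**Inputs from the protocol article.** 31 kindergartens per arm (Section 2.6); 1021 children, hence 1021/62 = 16.5 per kindergarten (Section 3); ICC 0.05 and significance level 0.05 (Section 2.7).

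**Assumptions not in the documents.** Two-sided testing, power 0.80, equal SDs at baseline and follow-up, the same ICC for every analysis, equal cluster sizes, complete follow-up, and the baseline-follow-up correlation r, shown as a range.

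**Step 1: relative variance.** In units of the follow-up variance:

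- change score: 2(1 − r)
- follow-up alone: 1
- follow-up adjusted for baseline: 1 − r²

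Adjusted over change is (1 − r²)/[2(1 − r)] = (1 + r)/2, below 1 for every r < 1. The change score is also worse than ignoring baseline when 2(1 − r) > 1, that is, when r < 0.5.

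**Step 2: detectable effect.** The design effect is 1 + (16.47 − 1) × 0.05 = 1.773. For follow-up alone the detectable effect is (1.96 + 0.84) × √(2 × 1.773/510.5) = 0.234 SD. Multiplying by the square root of the relative variances gives:

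| r (assumed) | Variance, change | Variance, adjusted | Ratio | Detectable, change | Detectable, adjusted |
|---|---|---|---|---|---|
| 0.3 | 1.40 | 0.91 | 0.65 | 0.276 | 0.223 |
| 0.5 | 1.00 | 0.75 | 0.75 | 0.234 | 0.202 |
| 0.8 | 0.40 | 0.36 | 0.90 | 0.148 | 0.140 |
| 0.9 | 0.20 | 0.19 | 0.95 | 0.104 | 0.102 |

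These use all 1021 children; the consent substudies are smaller.

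**Step 3: bias.** A simulated cluster trial (31 kindergartens per arm, 16 children each, ICC 0.05, true effect 0.200 SD, 4000 runs) gave a mean change-score estimate of 0.199 at r = 0.3, 0.5 and 0.9. Over randomisations there is no bias.

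**Step 4: given a baseline imbalance.** If the intervention arm starts d SD higher, the expected change-score error is −(1 − r)d. In the tenth of simulated trials with the largest imbalance in that direction:

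| r | Mean d | Formula: 0.200 − (1 − r)d | Simulated, change | Simulated, adjusted |
|---|---|---|---|---|
| 0.3 | 0.150 | 0.095 | 0.089 | 0.194 |
| 0.5 | 0.147 | 0.127 | 0.126 | 0.200 |
| 0.9 | 0.154 | 0.185 | 0.184 | 0.199 |

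The distortion is about half the effect at r = 0.3 and slight at r = 0.9.

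**The case against.** **The covariates may simply be unstated.** The Table 1 column gives model and response. Table 1(a) also lists no covariates, yet Section 2.7 adjusts the main outcomes, so a blank does not prove an unadjusted model, and a covariate list may sit in a fuller document. This stands in part: one may not conclude that age and sex adjustment is excluded for secondary outcomes, only that none is stated. It does not remove the point, because the change score itself is fixed in the table and, followed as written, has the properties shown above.

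**Regression to the mean.** A reader might infer that change scores leave a regression-to-the-mean bias in the intervention effect. The design does not support that. Randomisation makes the phenomenon act alike in both arms, and the simulated contrast is on target. Error arises only conditional on imbalance, whether by chance or through kindergartens lost after randomisation.

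**Sex mix.** Section 3 gives 247/511 = 48.3% boys in the control arm and 277/510 = 54.3% in the intervention arm. It is tempting to read this as a demonstrated bias. It is compatible with chance (p = 0.056 even ignoring clustering), mean age is 4.1 years in both arms, and differencing removes a constant sex difference in level. It supports adjustment as prudent and no more.

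**Counts.** That the loss is worst for the counts is plausible if they correlate weakly from year to year, but the documents give neither correlations nor distributions. A linear GEE with robust standard errors can validly estimate a difference in mean counts, so a count model is an option, not a correction of an invalid test.

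**Kindergarten environment.** Section 2.8 presents Table 1 as an overview of baseline analyses, so the baseline test may be descriptive, and a difference in a categorical item can be read as categories of change. Both readings are fair. What remains is that a baseline comparison between randomised arms carries no information on the intervention.

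**Exploratory status.** Section 2.7 declares the analyses explorative. This limits the consequence to lost precision and exposure to imbalance.

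**Conclusion.** The point holds as one of efficiency and robustness to imbalance, not validity. For the child-level secondary outcomes, the stated change-score model is less precise than adjusting follow-up for baseline at every correlation below one: the adjusted variance is 35% lower at r = 0.3, 25% at 0.5, 10% at 0.8 and 5% at 0.9. For strongly tracking measures, as anthropometry may be, the gain is small. Where r is below 0.5 the change score is worse than not using baseline at all. Conditional on a baseline imbalance of about 0.15 SD, it can misstate a 0.2 SD effect by roughly half at low r.

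The sizes rest on assumed correlations, equal SDs at both times and a common ICC. The ranking needs less: under the equal-SD model, adjustment is better for any r < 1.

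**What to change.** In Table 1(b), replace the change-score model for the child-level outcomes by a GEE of the follow-up value on arm and the baseline value of the same outcome, with size stratum, age and sex as covariates. If change is preferred for presentation, adding baseline to the existing model is enough: with an identity link, follow-up − baseline = a + b·arm + c·baseline rearranges to follow-up = a + b·arm + (c + 1)·baseline, so the arm effect b is the same. State explicitly in Section 2.7 that the adjustment extends to the secondary outcomes.

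For sick days, consultations, hospitalisations and parental absence, drop the continuous label and consider a log-link GEE (Poisson or negative binomial) with robust standard errors and the baseline count as covariate.

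For the kindergarten environment, compare arms at follow-up adjusted for baseline, for example by linear or logistic regression at kindergarten level with the size stratum. Report baseline values descriptively, and do not use the between-arm baseline test as evidence on the intervention.

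The cost is analysis-plan wording. Baseline values, age, sex and stratum are already collected; no extra measurement or participants are needed.
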